## Abstract

**Background:**

Palliative care is becoming increasingly important because the number of patients with an incurable disease is growing and their survival is improving. Previous research tells us that early palliative care has the potential to improve quality of life (QoL) in patients with advanced cancer and their relatives. According to limited research on palliative care in the Netherlands, patients with advanced cancer and their relatives find current palliative care suboptimal. The aim of the eQuiPe study is to understand the experienced quality of care (QoC) and QoL of patients with advanced cancer and their relatives to further improve palliative care.

**Methods:**

A prospective longitudinal observational cohort study is conducted among patients with advanced cancer and their relatives. Patients and relatives receive a questionnaire every 3 months regarding experienced QoC and QoL during the palliative trajectory. Bereaved relatives receive a final questionnaire 3 to 6 months after the patients’ death. Data from questionnaires are linked with detailed clinical data from the Netherlands Cancer Registry (NCR). By means of descriptive statistics we will examine the experienced QoC and QoL in our study population. Differences between subgroups and changes over time will be assessed while adjusting for confounding factors.

**Discussion:**

This study will be the first to prospectively and longitudinally explore experienced QoC and QoL in patients with advanced cancer and their relatives simultaneously. This study will provide us with population-based information in patients with advanced cancer and their relatives including changes over time. Results from the study will inform us on how to further improve palliative care.

**Trial registration:**

Trial NL6408 (NTR6584). Registered in Netherlands Trial Register on June 30, 2017.

## Background

Death comes to us all. In 2017, almost 47.000 people died of cancer in the Netherlands, which was with 31% the most common cause of death, followed by cardiovascular disease (25%) and mental disorders or diseases of the nervous system (14%) [1]. The number of people who die of cancer is relatively stable over time [2], despite increasing incidence of cancer and new treatment modalities in cancer, such as immunotherapies and targeted therapies. Fortunately, early detection and advances in cancer treatments have greatly improved survival. Consequently, the time patients live after their diagnosis of advanced cancer is prolonged and the number of patients diagnosed with advanced cancer has increased.

The disease trajectory of advanced cancer for patients is often depicted as a chronic illness, eventually followed by a steep decline and an inevitable death [3]. For relatives of patients with advanced cancer, the disease trajectory also includes a bereavement period after the death of a loved one. At some point in the advanced cancer trajectory, palliative care becomes important. Palliative care is an approach that provides prevention and relief of suffering by means of early identification and assessment and treatment of pain and other physical, psychosocial and spiritual problems [4]. Ideally, palliative care is timely and gradually integrated in oncological care so patients and relatives benefit most from palliative care services [3]. It is important that palliative care is timely integrated in standard oncological care because quality of life (QoL) is improved when patients with advanced cancer receive early palliative care [5–8].

Despite rapid developments [9], the integration and quality of palliative care in oncological care in the Netherlands could be further improved. Recent research shows that patients with advanced cancer are only reasonably satisfied with hospital care [10, 11]. This is worrisome, as the study by Engel et al. suggests that the experienced quality of care (QoC) and QoL may be positively associated. The effect evaluation of the Dutch National Quality Improvement Program Palliative Care showed that most patients and relatives are satisfied with palliative care, but improvements regarding psychosocial and spiritual support and post-bereavement care for relatives are needed [12]. Other research among relatives of patients who died in a University hospital showed that bereaved relatives reported a broad range of experiences, which suggest a widespread variance of the QoC [13]. For instance, Witkamp et al. showed that only 64% of bereaved relatives reported that they had been told that the patient’s death was imminent and 53% stated that the patients’ symptoms and problems in the last 24 h had been sufficiently alleviated. The same study found that according to bereaved relatives, only 42% of the patients had been sufficiently involved in medical decision making [13]. Unfortunately, solid and conclusive information on the experienced QoC and QoL in patients with advanced cancer and their relatives is scarce. Moreover, longitudinal research during the advanced cancer trajectory in patients and relatives is lacking.

A prospective longitudinal observational cohort study on experienced QoC and QoL in patients with advanced cancer and their relatives in the Netherlands is needed. This study will provide more insight into the care experiences, needs and QoL of patients with advanced cancer and their relatives that can guide us in improving daily oncological care and the integration of palliative care.

## Methods

### Aim

The aim of this study is to gain insight into the care experiences and QoL of patients with advanced cancer and their relatives. The following research questions will be addressed:
What is the experienced QoC according to patients with advanced cancer and their relatives?What is the experienced QoL in patients with advanced cancer and their relatives?Which factors are associated with the experienced QoC and QoL in patients with advanced cancer and their relatives?

### Study design

The study is a prospective longitudinal observational cohort study on experienced QoC and QoL in patients with advanced cancer and their relatives (eQuiPe study). Patients and their relatives are invited to complete questionnaires on experienced QoC and QoL every 3 months until death. Three to 6 months after a patient is deceased, the bereaved relative will receive a short final questionnaire. The survey data will be directly linked to the detailed clinical data routinely collected on patient characteristics, tumour characteristics, and treatment from the Netherlands Cancer Registry (NCR).

### Setting

The eQuiPe study is a nationwide study that is conducted in multiple hospitals (*n* = 40) in the Netherlands. Per hospital, the departments of medical oncology, pulmonology, and/or urology are participating in the study to identify eligible patients between November 2017 and January 2020.

### Study population

All patients with a diagnosis of a solid metastasized tumor (stage IV) are eligible for inclusion. Additional inclusion criteria are required for patients diagnosed with breast cancer and with prostate cancer to reduce variation and overrepresentation of patients with advanced cancer with a relatively good prognosis. Patients diagnosed with breast cancer are eligible when their metastases are located in multiple organ systems. Patients suffering from prostate cancer are eligible when their cancer is metastasized and castrate-resistant. These criteria are based on information regarding the mean survival time of these groups (NCR). Relatives of included patients, as chosen by the patient, will also be invited to participate in the study. Patients or relatives can participate in the study irrespective of the participation of the other. Patients are also allowed to invite more than one relative to participate in the study. Table 1 provides an overview of the inclusion and exclusion criteria.

**Table 1 Tab1:** Inclusion- and exclusion criteria

**Inclusion criteria:**	
Patients are eligible for inclusion if they are;	• diagnosed with (progression of) a solid tumour (stage IV) with metastases • additional criteria are in place for the following diagnosis: - breast cancer (stage IV with metastases in multiple organ systems) - prostate cancer (stage IV and Castrate-Resistant) • older than 18 years • able to complete a Dutch self-report questionnaire • able to understand the objective of the study and have signed the informed consent
Relatives of patients are eligible for inclusion if they are;	• indicated by the patient as relative • older than 18 years • able to complete a Dutch self-report questionnaire • able to understand the objective of the study and have signed the informed consent
**Exclusion criteria:**	
Patients and their relatives are excluded for participation in the study if;	• they suffer from dementia • they have a history of severe psychiatric illness

### Recruitment

Health care professionals of participating hospitals will identify patients who meet the inclusion and exclusion criteria. Health care professionals will hand out a patient information leaflet and ask eligible patients if they may be approached by the research team. The patient information leaflet will include comprehensive and understandable information regarding the study. Health care professionals will hand over the patients’ name and phone number to the research team after receiving consent from the patient, which is noted in the patient file or noted on a research sheet. These contact details will be given by phone, secured email or an online secured shared document, whichever route is preferred by the hospital. There is a possibility of self-referral for patients with advanced cancer and their relatives. Advertisement is spread via a Dutch online platform for patients and relatives who are confronted with cancer (www.kanker.nl). Patients and relatives can leave a contact request for the researcher. The recruitment procedure is similar for patients referred by their health care professional.

### Study procedures

#### Inclusion

A flowchart of the study procedures are presented in Fig. 1. Within a few days after receiving the patient’s contact information a researcher will phone the patient to explain the study and discuss participation. The patient is asked whether the researcher may approach one of his/her relatives. The relative is informed about the study via a similar procedure. When the patient and/or relative are willing to participate in the study, they are given the option to choose for the informed consent and questionnaires on paper or a web-based version via the Patient Reported Outcomes Following Initial treatment and Long-term Evaluation of Survivorship (PROFILES) registry [14].

**Fig. 1 Fig1:**
[figure not shown]
Flowchart of study process

#### Data collection

For the web-based version: after giving consent, participants will receive a letter that contains a link to a secure website (www.profielstudie.nl) where the patient can complete the web survey with their own login codes. The login codes are not directly linked to the patient. Patients who complete the online questionnaire can stop and save their data at each desired moment so they can continue the questionnaire at another time. If the participant prefers a paper version of the survey, they receive a paper version with a stamped self-addressed envelope to return the questionnaire to the researcher. If patients do not complete their questionnaire within 2 weeks, a reminder via email or letter will be sent, including the questionnaire. If the patient does not complete their questionnaire within 2 weeks after the reminder, they will be contacted by phone. A questionnaire regarding QoC and QoL will be sent in the same manner every 3 months, till participants indicate that they no longer want to participate in the study, or until death. After the death of a patient, the participating relative will receive our condolences by a personal postcard. Three to 6 months after the death of the patient, the participating bereaved relative will receive a final request to complete the last questionnaire regarding his or her experiences with care in the last phase of life of their loved one, QoL, the patient’s quality of death, and post-bereavement needs and support.

#### Questionnaires

A qualitative study was conducted (METC16.2050) to gather input from patients with advanced cancer and their relatives in the development of our questionnaire [15] ([name] et al: Shared persepctives of patients with advanced cancer and their informal caregivers on essential aspects of health care: a qualitative study, submitted). Participants of the focus groups and interviews shared their experiences regarding QoC and QoL, which helped us identify relevant themes for this cohort study. Therefore, the questionnaires involve many topics related to QoC and QoL that were raised by patients with advanced cancer and relatives themselves. Additionally, a systematic literature review was conducted to identify suitable and valid measurement instruments to use in our study [16]. Furthermore, the approved Dutch Quality framework regarding palliative care [17] has also been taken into account while selecting relevant measurement instruments for the eQuiPe study to maximize the comparability of our results. Subsequently, socio-demographic variables such as marital status, ethnicity, educational level, and religion were self-administered and added to the questionnaires. Table 2 provides an overview of all measurement instruments included in the study.

**Table 2 Tab2:** Overview measurement instruments and times points at which the questionnaires are administered during the study

Measurement	Measurement instrument	Baseline	Follow-up (every 3 months)	After patients’ death
***Patients***				
**Quality of care**	QLQ-IN-PATSAT32 [18], items CQ-index [19], items based on Dutch Quality framework Palliative Care [17]	X	X	
Health care consumption	Self-administered items	X	X	
Shared decision making	CPS [20], DEPS [21], Self-administered items	X	X	
Health care needs	PNPC-sv patient form [22]	X	X	
**Quality of life**	EORTC QLQ-C30 [23]	X	X	
Spiritual wellbeing	FACIT-sp [24]	X	X	
Social support	FACT-G scale [25]	X	X	
Use of social network	Self-administered item	X	–	
Sexual health	single items EORTC	X	X	
Body image	BIS [26]	X	X	
Relationship satisfaction^a^	Relationship ladder of the DAS [27]	X	X	
Illness perception	BIP [28]	X	X	
Individual coping	Brief COPE Inventory [29]	X	X	
Resilience	Connor-Davidson Resilience Scale [30]	X	X	
Dyadic coping^a^	DCI [31]	X	–	
Self-management	HeiQ [32]	X	–	
Depression	HADS depression scale [33]	X	–	
***Relatives***				
**Quality of care**	INPATSAT32 [18], CQ-index [19], items based on Dutch Quality framework Palliative Care [17]	X	X	–
Health care consumption	Self-administered items	X	X	
Health care needs	PNPC-sv caregiver form [22]	X	X	–
Evaluation of services	VOICES-SF [34], items based on Dutch Quality framework Palliative Care [17]	–	–	X
**Quality of life**	EORTC QLQ-C30 items [23]	X	X	X
Sexual health	single items EORTC	X	X	–
Social support	FACT-G scale [25]	X	X	X
Personal self-care	Personal Self-Care subscale of the SCPS [35]	X	X	X
Caregiver burden	ZARIT-12 [36], SRB [37]	X	X	–
Relationship satisfaction^a^	Relationship ladder from the DAS [27]	X	X	–
Individual coping	brief COPE Inventory [29]	X	X	–
Resilience	Connor-Davidson Resilience Scale [30]	X	X	–
Pre-death grief	Pre-death grief [38]	X	X	–
Dyadic coping^a^	DCI [31]	X	–	–
Circumstances of death	Self-administered items	–	–	X
Openness of communication about illness and death	CCID [39]	–	–	X
Impact of death	IES [40]	–	–	X

*Abbreviations*: *BIP* Brief illness perception, *BIS* Body image scale, *BMI* Body mass index, *CCID* Caregiver’s communication with the patient about illness and death, *CPS* Control preferences scale, *CQ-index* Consumer quality index, *DAS* Dyadic adjustment scale, *DCI* Dyadic coping inventory, *DEPS* Decision-making participation self-efficacy scale, *EORTC QLQ-C30* European organization for research and treatment of cancer quality of life questionnaire core 30 items, *FACIT-sp* Functional assessment of chronic illness therapy spiritual well-being, *FACT-G* Functional assessment of cancer therapy general, *HADS* Hospital anxiety and depression scale, *HeiQ* Health education impact questionnaire, *IES* Impact of event scale, *INPATSAT32* In-patient satisfaction with care measure 32 items, *PNPC-sv* Problems and needs in palliative care short form, *SCPS* Self care practices scale, *SRB* Self-rated burden scale, *VOICES-SF* Views of informal carers’ evaluation of services short form, *ZARIT-12* Zarit Burden

^a^ only provided to those patients and relatives with a partner

The questionnaires were tested on completion time, appropriateness, and burden in a pilot study (*n* = 31) among patients with advanced cancer and relatives. The pilot consisted of the ‘think-aloud’ method with six participants (two patients with advanced cancer, two relatives, and two bereaved relatives) and 15 participants gave postal feedback. Results of the pilot study indicated that the mean completion time for the most extensive questionnaire (baseline measurement for patients) was 38 min and completing the questionnaire was not experienced as a great burden, confrontational, incomprehensible, or inappropriate. Suggestions made by the participants of the pilot study were taken into account to further improve the questionnaire. Results from the pilot suggested that the questionnaire length is suitable for our study population. For patients who also participate in national tumor-specific cohort studies (PLCRC, POCOP, PACAP) [41], the questionnaires will be aligned and adjusted in order to decrease the response burden for participants.

#### PROFILES and NCR

PROFILES will be used for the logistics of the questionnaires. PROFILES is a registry for the study of the physical and psychosocial impact of cancer and its treatment from a dynamic, growing population-based cohort of people confronted with cancer. PROFILES follows the quality guidelines that are formulated in the ‘Data Seal of Approval’ document (www.datasealofapproval.org), developed by Data Archiving and Networked Services. The PROFILES registry is an ongoing data collection of patient reported outcomes within the sampling frame of the NCR and can be linked with clinical data of all individuals newly diagnosed with cancer in the Netherlands. For the eQuiPe study, socio-demographic and clinical data will be obtained from the NCR. Socio-demographic variables include date of birth, sex, and socio-economic status. Clinical data include cancer type, stage, and date of diagnosis.

### Study parameters

#### Main outcome

The main outcome of this study is the experienced QoC and QoL in patients with advanced cancer and their relatives. This includes all domains of QoL such as physical, psychological, social, and spiritual wellbeing.

#### Secondary outcomes

Secondary outcomes in this study are health care needs, shared decision making, and health care consumption of patients and relatives. Furthermore, social support, resilience, body image, sexual wellbeing, illness perception, individual coping, self-management, depression and use of social networks are measured (Table 2). Relatives will also receive questions on caregiver burden and personal self-care. For patients and relatives with a partner, also relationship satisfaction and dyadic coping will be assessed. In bereaved relatives, health care services in the last days of the patients’ life and aftercare will be evaluated. Furthermore, circumstances and impact of the patient’s death and the communication between relative and patient about illness and death are assessed.

### Statistical analysis

We aim for a large study population of approximately 1500 patients with advanced cancer and 1000 relatives. Including a large group of patients and relatives is necessary to assess the QoC and QoL of these participants at different time points in the palliative care trajectory and its course. A study sample of this size enables us to perform subgroup analyses, for example per age group, primary tumor site, cancer treatment, diagnosis, sex, and geographical region. Also, high dropout and lower response rates due to disease-related characteristics of our study population have to be taken into account. Due to the nature of this observational study, no sample size calculations haven been performed but the number of patients are based on annual incidence of advanced cancer in the Netherlands as recorded in the NCR.

All statistical analysis will be performed using statistical packages STATA version 16. For all analyses a two-sided significance level of *p* < 0.05 will be used. Descriptive statistics (frequencies, median, mean) will be used to analyze the experienced QoC, QoL, healthcare use, advance care planning, symptom burden of patients and relatives. Further, univariate analyses will be used to analyze the crude differences between subgroups regarding QoC or QoL using parametric tests, provided that the assumptions of these tests are met. If not, non-parametric tests will be used. When testing differences between subgroups, we will adjust for confounders which are theoretically relevant and statistically associated with the outcome variable of interest. Additionally, multi-level analyses will be used to analyze the primary and secondary outcomes over time.

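### Regional comparisons of care quality and quality of life are planned with tests that ignore hospital clustering, so their true error rate exceeds 5% by an amount that depends on an unstated ICC

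*Protocol article*

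**What the plan says.** The Setting section describes "a nationwide study that is conducted in multiple hospitals", with 40 hospitals given as the number. The target in the Statistical analysis section is "approximately 1500 patients with advanced cancer and 1000 relatives". The size is justified partly by the wish to analyse subgroups, for example "per age group, primary tumor site, cancer treatment, diagnosis, sex, and geographical region".

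For subgroup comparisons, the same section says that "univariate analyses will be used to analyze the crude differences between subgroups regarding QoC or QoL using parametric tests". This is conditional on the tests' assumptions being met; otherwise non-parametric tests are used. Differences are then adjusted for confounders that are relevant in theory and associated with the outcome. Multi-level analysis appears in the last sentence, for primary and secondary outcomes over time, and its levels are not named. One threshold covers everything: "For all analyses a two-sided significance level of *p* < 0.05 will be used".

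On relatives, the Study population section states that "Patients are also allowed to invite more than one relative to participate in the study". The Inclusion section describes the usual step: "The patient is asked whether the researcher may approach one of his/her relatives".

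**The concern.** Experienced quality of care is a main outcome, and patients recruited in one hospital are largely rating the same provider. Their scores are therefore likely to be correlated. All patients of a hospital would normally fall in the same region, so a regional contrast is a contrast between groups of hospitals. Its error should include the variation between hospitals. A t-test, one-way ANOVA or standard rank test on individual scores leaves that variation out.

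Neither further step in the plan repairs this. The rank-test fallback also assumes independent observations. Adding confounders does not supply a hospital error term, and hospital fixed effects cannot be used because region is constant within a hospital.

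The risk is that chance differences between hospitals are reported as regional differences in care. The Discussion expects conclusions that generalise across regions and care settings, and the Dissemination section offers the data for auditing and policy making, so such a result could be acted on.

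A smaller version of the problem arises among relatives. Two relatives of one patient share that patient and the care given, so they are not independent observations.

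**Working it through.** **The plan's own figure.** There is no power or precision calculation to reproduce: the article says that "no sample size calculations haven been performed". The only stated figure is the two-sided 0.05 level. With independent observations the formula below returns 0.050. A simulation with ICC 0 gave 0.054 for two regions and 0.052 for four.

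**Inputs from the article.** 1500 patients, 1000 relatives, 40 hospitals, two-sided 5%.

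**Derived.** 1500/40 = 37.5 patients and 1000/40 = 25 relatives per hospital, if all come from these hospitals in equal numbers.

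**Assumed, because the article gives no value.** The hospital ICC, the number of regions, the share of relatives who take part in pairs, and the correlation within a pair.

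**Formulas.**
- Design effect: DE = 1 + (m − 1) × ICC, where m is the number per hospital.
- True error, two regions: 2 × [1 − Φ(1.96/√DE)].
- True error, k regions: P(χ² with k − 1 df > c/DE), where c is the 95% point of that distribution.
- Ratio of honest to naive interval width: √DE. Effective sample size: 1500/DE.

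**Patients, m = 37.5.** For example, at ICC 0.02, DE = 1 + 36.5 × 0.02 = 1.73.

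| Assumed ICC | DE | Error, 2 regions | Error, 4 regions | Interval ratio | Effective n |
|---|---|---|---|---|---|
| 0.005 | 1.18 | 0.071 | 0.085 | 1.09 | 1268 |
| 0.01 | 1.365 | 0.093 | 0.126 | 1.17 | 1099 |
| 0.02 | 1.73 | 0.136 | 0.211 | 1.32 | 867 |
| 0.05 | 2.825 | 0.244 | 0.429 | 1.68 | 531 |

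**Simulation check.** One-way ANOVA with 40 hospitals of 38 patients, 4000 runs each, gave 0.090, 0.142 and 0.256 for two regions at ICCs of 0.01, 0.02 and 0.05. For four regions it gave 0.127, 0.211 and 0.451. These agree with the formulas.

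**Unequal hospitals.** With a coefficient of variation of 0.6 in hospital size (assumed), DE = 1 + (1.36 × 37.5 − 1) × ICC = 1 + 50 × ICC. The two-region error is then 0.110, 0.166 and 0.295 at ICCs of 0.01, 0.02 and 0.05, so equal sizes are the favourable case.

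**Relatives, m = 25, hospital clustering only.** The two-region error is 0.064, 0.078, 0.107 and 0.186 at ICCs of 0.005, 0.01, 0.02 and 0.05.

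**Factors that vary within hospitals.** A two-level factor spread at random within hospitals, as sex roughly would be, gave simulated error of 0.046 to 0.052 for ICCs of 0.01 to 0.10. There is no inflation.

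**Several relatives per patient.** If a share s of relatives take part in pairs with correlation ρ, then DE = 1 + s × ρ for a factor that both members share. With s = 0.10 and ρ = 0.4, DE = 1.04 and the error is 0.055. With s = 0.40 and ρ = 0.6, DE = 1.24 and the error is 0.078.

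**After the change.** A t-test on hospital means, which for equal hospital sizes corresponds to a hospital random intercept, gave simulated error of 0.051, 0.052 and 0.045 at ICCs of 0.01, 0.05 and 0.10.

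**The case against.** The strongest reply is that the article nowhere says that clustering will be ignored. It makes the parametric tests conditional on their assumptions, independence is one of those, and multi-level models are named without their levels. The article is a condensed protocol, and random-effect structure is often left to an analysis plan. This stands in part: a reader should not infer that the authors decided to assume independence. But the article does fix the subgroup test, its fallback, the adjustment and the use of multi-level models. Followed as written, none of the subgroup steps has a hospital term, and the stated remedy for failed assumptions leads to tests that need independence too.

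Four stronger readings are tempting and are not supported:

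- **That subgroup testing in general is invalid.** Of the six example factors, only region is plainly a between-hospital factor. Factors balanced within hospitals keep their nominal error. Tumour site lies in between: departments take part selectively, so site may partly follow the hospital.
- **That regional tests are shown to reject far too often.** No ICC, number of regions or allocation of hospitals to regions is given. At an ICC of 0.005 to 0.01 the two-region inflation is modest; it becomes severe only towards 0.05.
- **That the article contradicts itself on the number of relatives.** Asking to approach one relative is compatible with letting the patient invite others. One appears to be the default, and the effect of pairs is small in most of the range examined.
- **That the change needs nothing but new wording because hospital is already recorded.** The article does not confirm this. Hospital is not among the NCR variables listed under PROFILES and NCR, and the Recruitment section allows self-referral through an online platform.

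Self-referral, and the Discussion's wording that 40 hospitals have joined so far, also make 37.5 per hospital an approximation.

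**Conclusion.** The point holds for geographical region and for any other factor that varies between hospitals. For these, the stated tests exceed 5% at any positive hospital ICC. The excess could be slight or serious: in the two-region case it runs from about 2 to about 19 percentage points over assumed ICCs of 0.005 to 0.05, and it grows with the number of regions and with unequal hospital sizes. The direction is certain given positive correlation within hospitals; the size is not, because it rests on assumed ICCs and on an even spread of 1500 patients over 40 hospitals. The corresponding issue for several relatives of one patient is real but minor. The change is worth making because the method is stated, region is a named use of it, and a better method is available at low cost.

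**What to change.** State in the Statistical analysis section that comparisons by region, and by any other hospital-level factor, will use one of two methods, in crude and adjusted analyses alike:

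- a mixed model with a random intercept for hospital and small-sample degrees of freedom, or
- regression with a variance that is robust to clustering by hospital.

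The planned tests can stay for factors that vary within hospitals, although using the same model throughout would be simpler. In relatives' analyses, add a patient-level random effect or cluster on the patient where more than one relative takes part. Say in the Inclusion section that the single approach does not exclude further relatives invited by the patient.

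Two costs should be accepted openly. Intervals for regional contrasts become about 17%, 32% or 68% wider at ICCs of 0.01, 0.02 or 0.05; that width reflects uncertainty which the ordinary tests leave out. Hospital must also be available in the analysis data, with a stated rule for self-referred participants, for example assignment to their treating hospital if it is known and a sensitivity analysis without them if it is not. The change needs no new design and no extra recruitment.
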